# Efficacy and safety comparison of infrared laser moxibustion and traditional moxibustion in knee osteoarthritis: study protocol for a Zelen-design randomized controlled non-inferiority clinical trial

**DOI:** 10.1186/s13018-023-04408-x

**Published:** 2023-12-02

**Keywords:** Moxibustion, Infrared laser moxibustion, KOA, Non-inferiority, Randomized controlled trial

## Abstract

**Background:**

Knee osteoarthritis (KOA) is the most common chronic degenerative joint disease and places a substantial burden on the public health resources in China. The purpose of this study is to preliminarily evaluate whether infrared laser moxibustion (ILM) is non-inferior to traditional moxibustion (TM) in the treatment of KOA.

**Materials and methods:**

In the designed Zelen-design randomized controlled non-inferiority clinical trial, a total of 74 patients with KOA will be randomly allocated to one of two interventions: ILM treatment or TM treatment. All participants will receive a 6-week treatment and a follow-up 4 weeks after treatment. The primary outcomes will be the mean change in pain scores on the numeric rating scale (NRS) measured at baseline and the end of last treatment at week 6. The secondary outcomes will be the pain scores on the NRS from weeks 1 to 5 after the start of treatment and the changes from baseline to endpoints (weeks 6 and 10) in the Western Ontario and McMaster Universities Osteoarthritis Index (WOMAC), SF-36, knee circumference, and 6-min walking test. In addition, safety assessment will be performed throughout the trial.

**Conclusion:**

The results of our study will help determine whether a 6-week treatment with ILM is non-inferior to TM in patients with KOA, therefore providing evidence to verify if ILM can become a safer alternative for TM in clinical applications in the future.

*Trial registration*: Clinical Trial Registration Platform (ChiCTR2200065264); Pre-results. Registered on 1 November 2022.

**Supplementary Information:**

The online version contains supplementary material available at 10.1186/s13018-023-04408-x.

## Introduction

Osteoarthritis (OA) is one of the most common chronic degenerative joint diseases caused by abnormal metabolism of joint tissues. It usually manifests as early onset pain, followed by stiffness, swelling, injury of periarticular tissue, limited activity and deformity [1, 2], all of which can affect the patient’s quality of life [3, 4]. As one of the primary load-bearing joints, the knee is frequently affected by OA. In China, due to the aging population and economic development that has led more people to seek medical treatment, and the occurrence rate of knee Osteoarthritis (KOA) has been increasing annually from 2008 to 2017. Moreover, KOA is no longer exclusive to the elderlies, an increasing number in the younger population are also suffering from this disease, and all of which yield to a substantial burden on the public health resources in China [5].

In the early stages of KOA, it should be treated conservatively with the primary goal of alleviating joint pain in mild to moderate KOA [6]. Pharmacological therapies including non-steroidal anti-inflammatory drugs, acetaminophen, glucosamine, and chondroitin sulfate only can provide temporary pain relief in addition to having toxic side effects [7, 8]. The recommended safe and long-term measures, which include patient education, physical exercise, and weight management, are mostly preventive and relatively difficult to implement [9, 10].

Traditional moxibustion (TM) is a commonly used alternative therapy for KOA in Asia [11, 12]. The efficacy of TM is considered to result from a combination of factors [13–15], among them, near-infrared (NIR) light is generally thought to play a major role in the biological radiation effect of moxibustion. The NIR radiation can induce active substances to promote the metabolism and thermogenesis of the organs reached by the NIR rays, thereby adjusting the body’s immune and neurological functions by energizing cell metabolism [16–18]. Other studies indicated that photobiomodulation plays an active role in anti-inflammatory and analgesia [19, 20]. In recent years, the Chinese regime has been greatly emphasizing on the integration of traditional Chinese medicine (TCM) instruments with modern science and technology, and some novel moxibustion instruments have been developed to minimize the adverse effects of TM while maintaining its effectiveness [21–24]. However, the currently available instruments have two major problems: (1) the working temperature is much lower than the burning temperature of natural moxa pillars; and (2) the characteristics of moxibustion burning infrared spectrum have not yet compiled a unified standard, so none of these instruments can actualize a high simulation of the natural moxibustion emission spectrum and hindering the therapeutic effects.

For the above reasons, we will set up an infrared emissivity test system to accurately test for a reliable basic data of moxibustion emission spectrum, and then regulate the emission spectrum of the material by regulating the composition structure of infrared ceramics/graphene to realize the coupling between it and the absorption spectrum of human acupoints [25]. On this basis, we use a Mg–ZrO2/ graphene specified composite ceramic block as the key material of emission light source to develop infrared laser moxibustion (ILM). Therefore, we designed a Zelen-design randomized controlled non-inferiority clinical trial to (1) preliminarily investigate whether ILM is non-inferior to TM in reducing pain and improving function in patients with KOA; and (2) provide clinical evidence to verify whether ILM can become a safe and reliable clinical alternative to TM in the future.

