### Sample size calculation

This study is a randomized controlled non-inferior trial. Based on the literature, the smallest clinically significant difference in the pain NRS is 2 points [44–46]. Thus, we set the non-inferiority margin to − 2. The NRS score of the subjects after treatment was taken as the main outcome index. According to the results of similar studies, [47] the average NRS score of the experimental group was 40.53 ± 26.63, and that of the control group was 41.58 ± 15.07. So we used PASS 15 to calculate the sample size (29 participants in each group), *α* = 0.025, 1 − *β* = 80%. Considering that a maximum of 25% dropped out during the trial, we ultimately plan to recruit 74 participants (37 in each group) to ensure the target sample size is obtained. The calculation results of sample size are provided as Additional file 2.

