### Statistical analysis

Statistical analysis will be undertaken using both intention-to-treat (ITT) and per-protocol (PP) analyses. For the ITT analysis, all patients who undergo the Zelen-type randomization and received at least one treatment will be analyzed. Primary PP data analysis will also be undertaken for all patients who have high compliance (patient compliance rates equal to or greater than 80%) and do not use drugs or treatments prohibited by the protocol during treatment.

The statistical analysis will take the form of a non-inferiority test. The margin of non-inferiority is -2. For the main outcome, we will calculate the 95% confidence interval for the difference in NRS pain score between the treatment group and the control group. If the lower limit is greater than -2, non-inferiority will be considered valid.

For continuous data, mean ± standard deviation will be used to describe data that conforms to a normal distribution, whereas non-normally distributed continuous data will be described as the median (interquartile spacing). Where the data conforms to a normal distribution, independent sample t-test will be used for comparison between the two groups with homogeneity of variance; otherwise, a t-test will be used with heterogeneity of variance. Wilcoxon rank-sum test will be used if data does not conform to a normal distribution. Categorical data will be represented by frequency or percentage and compared using chi-square test or Fisher exact test. Missing data will be replaced according to the last observation carried forward method. The 95% confidence interval will be calculated, and *P* < 0.05 will be considered to indicate a significant difference. All statistical analysis will be performed using SPSS software (version 20.0).

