The results of our study will help preliminarily determine whether the infrared ceramic graphene moxibustion device is non-inferior to traditional moxibustion in alleviating knee pain and improving related function in KOA patients, therefore providing a suitable alternative for TM in clinical practice. In the future, based on the results of this exploratory study, we hope to design and carry out a multicenter, large-sample, randomized controlled clinical trial with a longer follow-up period to confirm the results and enhance the generalizability of the findings.

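### Non-inferiority is aimed at and concluded for function as well as pain, but the only margin and decision rule are for NRS pain

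*Protocol article*

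**What the plan says.** **Aim and conclusion.** The Introduction gives the first aim as to "preliminarily investigate whether ILM is non-inferior to TM in reducing pain and improving function in patients with KOA". The Discussion closes by expecting results that help determine, preliminarily, whether the device is "non-inferior to traditional moxibustion in alleviating knee pain and improving related function in KOA patients". Both put function under the non-inferiority claim.

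**Margin and rule.** Sample size calculation takes 2 points as the smallest clinically significant NRS difference and continues: "Thus, we set the non-inferiority margin to − 2". Statistical analysis says the analysis will be a non-inferiority test with that margin, then applies it to one outcome: "For the main outcome, we will calculate the 95% confidence interval for the difference in NRS pain score between the treatment group and the control". Success is declared when the lower limit lies above −2.

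**Function outcomes.** Secondary outcomes lists WOMAC and 6MWT, with SF-36 and knee circumference, as changes from baseline to weeks 6 and 10. For continuous data, Statistical analysis gives t-tests or the Wilcoxon rank-sum test. It adds that a 95% confidence interval will be calculated and that P < 0.05 "will be considered to indicate a significant difference".

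**Safety.** The second aim is to "provide clinical evidence to verify whether ILM can become a safe and reliable clinical alternative to TM in the future". The abstract's conclusion is phrased comparatively: "therefore providing evidence to verify if ILM can become a safer alternative for TM in clinical applications in the future". Safety assessment describes recording adverse events, laboratory tests and monitoring. It names no between-group safety hypothesis.

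**The concern.** A non-inferiority claim needs a margin fixed in advance on the scale of the outcome, and a rule that sets a confidence limit against it. For function the document makes the claim in its aim and its conclusion but supplies neither element. What it does supply for such outcomes is a test of no difference. A significant result there shows a difference. A non-significant result shows only that the data did not exclude zero, which is compatible with a material deficit in a trial of this size.

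At stake is the second half of the first aim. Followed as written, the plan can answer the pain question, but no result on WOMAC or 6MWT would entitle the authors to the function wording in the Discussion.

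**Working it through.** **1. Which outcome the trial was sized for.** Inputs from Sample size calculation: margin 2, α = 0.025 (taken as one-sided), power 80%, SDs 26.63 and 15.07. Assumptions needed to reach the stated 29: SDs divided by 10 to fit a 0–10 scale, the larger SD (2.663) in both arms, true difference 0.

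- Normal formula: n = 2 × SD² × (1.960 + 0.842)² / margin² = 2 × 7.092 × 7.849 / 4 = 27.8, so 28 per arm.
- Noncentral t: power is 0.788 at 28 and 0.802 at 29, so 29 per arm.

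The stated 29 follows from pain inputs alone. Nothing in it concerns function.

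**2. Whether the margin can be carried over.**

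| Outcome | Unit | Worse direction | Margin stated |
|---|---|---|---|
| Pain NRS | points, 0–10 | higher | −2 |
| WOMAC | sum over 24 items | higher | none |
| 6MWT | distance walked | lower | none |

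Two NRS points have no meaning as WOMAC points or as metres. WOMAC and 6MWT also run in opposite directions, so a single requirement that the lower limit exceed −2 cannot serve both.

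**3. What a non-significant difference test would mean.** No function SD is given, so the true deficit d is assumed in SD units. For a two-sided 0.05 t-test, noncentrality = d × √(n/2), with 2n − 2 degrees of freedom.

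| True deficit | n per arm | Noncentrality | P(not significant) |
|---|---|---|---|
| 0.3 SD | 29 | 1.142 | 0.798 |
| 0.3 SD | 37 | 1.290 | 0.753 |
| 0.5 SD | 29 | 1.904 | 0.535 |
| 0.5 SD | 37 | 2.151 | 0.436 |

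A normal approximation gives 0.793, 0.748, 0.522 and 0.424, so the method matters little.

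**4. What a function margin would require.** With one-sided 0.025, true difference 0 and the normal approximation, the margin that gives 80% power is (1.960 + 0.842) × √(2/n): 0.74 SD at 29 per arm and 0.65 SD at 37. For an assumed margin of 0.5 SD, power is 48% at 29 and 58% at 37, and 80% power needs 63 per arm. For 0.3 SD, power is 21% and 25%, and 175 per arm are needed.

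**5. Safety wording.** Statistical analysis compares categorical data by chi-square or Fisher exact test, and this can be applied to adverse-event frequencies. At 37 per arm, Fisher P < 0.05 needs 6 TM patients with an event against 0 on ILM (P = 0.025), or 9 against 2 (P = 0.046). With assumed rates for TM and ILM, Fisher power is 14% for 20% against 10%, 49% for 30% against 10%, and 82% for 40% against 10%. A comparison is available, but it would detect only a large difference.

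**The case against.** **The wording is hedged and function is secondary.** The aim and the conclusion are both preliminary, the Discussion calls the study exploratory, and a larger trial is to follow. This stands and lowers the severity. It does not supply a margin.

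**Secondary margins may be in an analysis plan that is not shown.** Their absence alone would be no finding. The point here is that this document states a two-part aim and conclusion and ties its decision rule to one part.

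**Confidence intervals are already planned.** True. The sentence with the P < 0.05 rule also provides for a 95% interval, so the function outcomes are not left with P values alone. Without a margin, however, an interval estimates the difference and cannot decide non-inferiority.

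**The general sentence on a non-inferiority test covers everything.** It carries only the −2 margin, which step 2 shows does not transfer.

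**Stronger readings.** A reader might infer that a non-significant function result will be reported as non-inferiority. Nothing in the document says so, and its only non-inferiority rule is the interval for the main outcome. The percentages in step 3 show what such a reading would risk, not what the authors plan.

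A reader might also infer that the trial aims to prove ILM safer and has no comparison that could show it. The aim says only safe and reliable. The comparative word occurs in the abstract's conclusion, as something ILM might become. The chi-square or Fisher rule can compare adverse-event frequencies. Not sizing a trial for safety is usual and is no error.

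**Conclusion.** The point holds for function and is one of severity CONSIDER. The non-inferiority aim and conclusion extend to function, while the only margin and the only decision rule concern NRS pain. The comparisons described for WOMAC and 6MWT cannot establish non-inferiority. The pain half of the first aim has its margin and rule and is not touched by this point.

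The mismatch rests on the text alone and needs no assumption. Its illustrated size, non-significance in about 44–54% of trials with 37–29 per arm under a 0.5 SD deficit, depends on the assumed deficit, equal SDs and approximate normality. On safety only a minor wording difference remains between the abstract and the stated aim.

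**What to change.** - In the Introduction and Discussion, restrict the non-inferiority aim and conclusion to NRS pain at week 6.
- Report WOMAC function and 6MWT as between-group differences in change from baseline with 95% confidence intervals, and without non-inferiority wording.
- Alternatively, before unblinding, fix and justify a margin with its direction for one named function outcome, and test it only after pain has met its rule. Step 4 shows that power would be limited unless that margin is wide.
- As a minor wording point, align the abstract's comparative safety phrase with the safe and reliable wording of the aim. Present adverse-event proportions by group with confidence intervals.

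The cost is a narrower claim and a few changed sentences. Sample size, visits, treatment and the primary analysis stay as they are.

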## Methods

### Study design

The Zelen-design randomized controlled non-inferiority clinical trial will be conducted at Beijing Electric Power Hospital of the State Grid Corporation of China and AMHT Group Aerospace 731 Hospital. The trial protocol is in accordance with the SPIRIT guidelines and the CONSORT guidelines, [26, 27] and the above two checklists are provided as Additional file 1. This trial was approved by the Beijing University of Traditional Chinese Medicine on 17 October 2022 (Ethics Reference No: 2022BZYLL1017). In view of the ethical requirements of current clinical trials, the schedule of recruitment, randomization, informed consent, intervention, and assessment are shown in Fig. 1.

**Fig. 1 Fig1:**
[figure not shown]
Flow chart *KOA*, knee osteoarthritis; *TM*, traditional moxibustion; *ILM*, Infrared laser moxibustion

### Trial status

This clinical trial is currently recruiting patients. Enrollment started in November 2022 and is expected to be completed by November 2023.

### Participants

Recruitment will be facilitated by the outpatient departments of the two hospitals and advertising on the We Chat platform. All treatments, assessments, blood tests, and knee X-rays will be provided free of charge. And at the end of the study, we will provide participants with a subsidy based on each patient’s degree of cooperation.

### Inclusion criteria

The inclusion criteria were as follows:Diagnosed with KOA according to the American College of Rheumatology criteria [28].Aged 40–70 years old.Average pain score of 4 or more out of 10 on the numeric rating scale (NRS) [29].Average severity score of 48 or less on the Western Ontario and McMaster Universities Osteoarthritis Index (WOMAC) [30].Standard radiographs with Kellgren–Lawrence (KL) grade II or III [31].Written informed consent.With basic reading and comprehension skills.

Participants who fulfill the above seven criteria can be included in the trial.

### Exclusion criteria

The exclusion criteria were as follows:Received knee surgery in the past six months or waiting for surgery.Received acupuncture treatment for KOA in the past three months.Received an intra-articular injection for KOA in the past six months.Received arthroscopy for KOA in the past year.Had other diseases, infections, or traumatic injuries that could cause knee pain.Had serious cardiovascular and cerebrovascular, respiratory, liver, kidney, metabolic system and other diseases, malignant tumors, mental disorders.Allergic to moxibustion smoke or infrared light.Pregnant or lactating.Received other similar physiotherapy methods in the past month.

Participants who met at least one of the exclusion criteria above will be excluded from the trial.

### Randomization and informed consent

A single-consent Zelen design will be used for allocation and randomization. An independent statistician will generate a random number table using the statistical software SPSS20.0, and the random seed will be set in advance. Each subject’s random number and treatment will be hidden in an opaque envelope. After enrollment assessment, all eligible participants will obtain an envelope in the order of entry.

All participants who meet the inclusion criteria will be randomly assigned to the TM group (the proposed control group) or the ILM group (the proposed treatment group) in a 1:1 ratio. Participants in the ILM group will be asked if they are willing to comply with the current randomized treatment; if they agree, they will be placed in the ILM group; if not, they will be automatically placed in the TM group. Participants in the TM group were directly enrolled without the above questioning process [32, 33], all participants will sign informed consent forms before enrollment [34].

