This study will be the first clinical trial to evaluate infrared ceramic/graphene laser moxibustion for the treatment of KOA. The study will test the hypothesis that ILM is not inferior to TM for the treatment of KOA. The Zelen-design adopted in this study is consistent with the real diagnosis and treatment environment, thereby minimizing the bias inherent in the traditional design of randomized controlled trials. During the trial, the willingness of patients or their guardians receive different treatments will be considered to help ensure the compliance of patients and the smooth conduct of the trial.

The primary priority in the treatment of KOA is pain relief followed by maintaining normal knee function and improving quality of life; thus, we chose pain on the NRS as the primary outcome and WOMAC, SF-36, knee circumference, and 6MWT as the secondary outcomes. For the safety evaluation, in addition to recording AEs, we will also conduct blood routine and CRP detection before and after the trial. CRP is one of the most commonly used laboratory indicators of systemic inflammatory diseases. The expression of CRP increases in patients with OA and is closely related to the progression and prognosis of the disease [50, 51].

The proposed study has some limitations that should be acknowledged. First, this is a non-inferiority trail; thus, compared with superiority trials, some participants may have greater difficulty adhering to the protocol for their treatment. This may result in incorrectly rejecting the null hypothesis [50]. For this reason, the Zelen-design was used to improve patient compliance. Second, it is difficult to blind the researchers involved in the assignment and treatment due to the differences in the nature of the treatments. Therefore, to reduce the risk of bias, the study evaluation will be conducted by people not involved in assignment or treatment. Third, this will be a small-scale trial with a small sample size. Finally, this study will primarily use subjective scales to evaluate knee joint pain and function; objective physiological indicators are lacking.

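### ILM refusers are given TM, but neither analysis set as worded settles how they are analysed, so the 2.5% error rate of the non-inferiority test is not assured

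*Protocol article*

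**What the plan says.** The protocol article describes a single-consent Zelen design with 1:1 allocation (Randomization and informed consent). Patients randomised to ILM are asked whether they will take it; "if not, they will be automatically placed in the TM group". The other arm is not asked: "Participants in the TM group were directly enrolled without the above questioning process". Crossover can therefore run only from ILM to TM.

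The Statistical analysis section sets out two analyses: "Statistical analysis will be undertaken using both intention-to-treat (ITT) and per-protocol (PP) analyses".

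- **ITT:** "all patients who undergo the Zelen-type randomization and received at least one treatment will be analyzed". The arm in which a refuser is counted is not given, and the one treatment need not be the allocated one.
- **PP:** "all patients who have high compliance (patient compliance rates equal to or greater than 80%) and do not use drugs or treatments prohibited" under the plan. The text does not say which treatment compliance is measured against, and TM is a trial treatment, not a prohibited one.

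Non-inferiority is claimed if the lower limit of the 95% confidence interval lies above −2. No sentence says in which set, or whether in both.

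The Discussion accepts that poor adherence in a non-inferiority trial can lead to wrong rejection of the null hypothesis, and then says: "For this reason, the Zelen-design was used to improve patient compliance".

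**The concern.** In a non-inferiority trial, anything that makes the two arms more alike favours a positive result. An ILM-randomised patient who receives TM does this if counted as ILM. Counting the same patient as TM avoids the dilution, but the groups are then formed partly by patient choice, and only on one side.

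A PP set normally gives some protection against dilution. Here, a refuser who attends at least 80% of TM sessions and takes nothing prohibited meets the PP wording on its plain reading.

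The Discussion offers the Zelen design as protection against wrongly rejecting the null. For patients who accept their treatment it may help. For refusers analysed as randomised it produces the very non-adherence that the Discussion warns of.

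What is at stake is who is compared with whom in the primary test, and whether its one-sided 2.5% error rate is held.

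**Working it through.** **Inputs**

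- Margin 2 points; lower 95% limit must exceed −2 (Statistical analysis). I read the difference as pain reduction, ILM minus TM, so that −2 is the unfavourable side.
- α = 0.025 (taken as one-sided), power 80%, 29 per group, 37 with the dropout allowance (Sample size calculation).
- SDs 26.63 and 15.07 (same section). Assumption: these are on a 0–100 scale, so 2.663 and 1.507 on the 0–10 NRS. Their root mean square is √((2.663² + 1.507²)/2) = 2.164.
- Refusal share *r* among ILM patients: not given. Assumed 5% to 30%.
- Refusers respond to TM as TM patients do (assumption, relaxed in step 3).

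**Step 1. The plan's own figure.** With SD 2.663 in both arms and no true difference, the normal formula gives 2 × 2.663² × (1.960 + 0.842)² / 2² = 27.8, so 28. With the non-central t at n = 29: SE = 2.663 × √(2/29) = 0.699, shift 2/0.699 = 2.86, 56 df, power 0.80. So 29 is reproduced, and 29 × 1.25 = 36.25 gives 37. SD 2.663 is therefore the main case.

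**Step 2. Refusers analysed as randomised.** Let ILM truly be worse by exactly 2. The expected deficit shrinks to 2(1 − *r*). False non-inferiority = P(T > t₀.₉₇₅), with T non-central t on 2n − 2 df and shift 2*r*/SE. Example: *r* = 0.2, n = 29: 0.4/0.699 = 0.572, giving 0.081.

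| *r* | Expected deficit | SD 2.663, n = 29 | SD 2.663, n = 37 | SD 2.164, n = 29 | SD 2.164, n = 37 |
|---|---|---|---|---|---|
| 0 | 2.0 | 0.0250 | 0.0250 | 0.0250 | 0.0250 |
| 5% | 1.9 | 0.0344 | 0.0359 | 0.0370 | 0.0389 |
| 10% | 1.8 | 0.0466 | 0.0504 | 0.0533 | 0.0585 |
| 20% | 1.6 | 0.0811 | 0.0930 | 0.1024 | 0.1199 |
| 30% | 1.4 | 0.1321 | 0.1577 | 0.1783 | 0.2168 |

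The larger SD gives the smaller inflation, so the main case is the cautious one.

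**Step 3. Other ways to count refusers.** Simulation, 10,000 runs per setting, 29 per arm, SD 2.164, true deficit 2, 20% refusal. Entries are the probability of false non-inferiority.

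| Refusers' improvement relative to others | As randomised | Counted in TM | Excluded from PP |
|---|---|---|---|
| 1 point less | 0.099 | 0.078 | 0.050 |
| Same | 0.093 | 0.023 | 0.023 |
| 1 point more | 0.091 | 0.005 | 0.010 |

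The simulated 0.093 is a little below the 0.102 of step 2 because mixing two response levels widens the spread in the ILM arm.

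**Step 4. Power of a PP set without refusers.** With 20% refusal, 37 × 0.8 = 29.6, about 30 ILM patients. For 30 v 37: SE = 2.663 × √(1/30 + 1/37) = 0.654, shift 3.06, power 0.85. At the planned evaluable number, 29 × 0.8 = 23.2; for 23 v 29: SE = 0.744, shift 2.69, power 0.75. Taking 25% off 30 and 37 gives 22.5 and 27.75; at 22 v 28, power is 0.73.

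**The case against.** The strongest reply is that the text is ambiguous rather than wrong. Being placed in the TM group may mean analysis there, in which case nothing is diluted. The randomisation section speaks of willingness to comply with the randomised treatment. If compliance in the PP definition carries that sense, a refuser has none and is already excluded. The statistical section also attaches the word primary to the PP analysis, and a fuller plan may settle precedence. Requiring at least one treatment is a common modified ITT. Finally, the inflation figures rest on refusal rates that the article does not give; with no refusals there is no effect.

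Much of this stands. A reader might infer that the trial is bound to drift towards a false claim of non-inferiority. The documents do not support that: dilution follows only from analysis by randomised arm, and step 3 shows that counting refusers in TM can raise or lower the error. Nor can it be said that PP certainly keeps refusers, only that its wording does not exclude them. The loss of untreated patients is minor and cannot be sized, although it could differ between arms because only one is asked.

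What does not stand is leaving it all to an unseen plan. The article itself states the crossover, both sets and the decision rule, and as stated they do not fit together. The word primary before PP does not say which set must meet the margin.

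A reader might also infer that, since "all participants will sign informed consent forms before enrollment", willingness to take ILM should be asked before the envelope is opened. That would give up the chosen Zelen design when enrolment was due to finish in November 2023. It is a trade-off, not a correction, and is not proposed here.

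**Conclusion.** The concern holds in this form: the crossover is one-way into the comparator, and neither set as worded assigns or removes refusers. Under analysis by randomised arm, the usual meaning of ITT, the one-sided error at a true 2-point deficit rises from 2.5% to about 5% at 10% refusal, 8–9% at 20% and 13–16% at 30% (SD 2.66, 29–37 per arm). This assumes that refusers respond as TM patients do, equal SDs, and refusal rates that are mine and not the plan's. Under analysis in TM, error stays near 2.5% if refusers have average prognosis, but runs from 0.5% to 7.8% at 20% refusal if they improve 1 point more or less than others (SD 2.164). The direction is then unknown and randomisation no longer protects the comparison. The Discussion's suggestion that the Zelen design guards against wrongly rejecting the null does not hold for this crossover. The wording should be settled before analysis.

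**What to change.** In the Statistical analysis section:

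1. ITT: every randomised patient, in the randomised arm, treated or not.
2. PP: patients who received at least 80% of the sessions of their randomised treatment and nothing prohibited, so that ILM refusers are excluded. With three sessions a week for six weeks, 0.8 × 18 = 14.4, that is, at least 15 sessions.
3. Non-inferiority is claimed only if the 95% confidence interval meets the margin in both sets.
4. The number of ILM refusers is reported.

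In the Discussion, say that the design may help compliance among those who accept their treatment, but that refusals create one-way crossover, which can favour non-inferiority in the ITT analysis.

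These are wording changes; recruitment and treatment stay as they are. There are three costs. At 20% refusal and SD 2.66, PP power is about 85% before dropout (30 v 37) and about 75% after it (23 v 29), below the planned 80%; requiring both sets cannot raise it. Excluding refusers is itself open to selection (error 1.0% to 5.0% in step 3), which is why PP should not decide alone. Untreated patients brought into ITT need a week-6 score where one can be obtained, because the planned last-observation rule would give them zero change.
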